#### Exclusion Criteria

- Unclear legal custody status of both parents- Infant has end-of-life care pathway- Infant died before recruitment.

### Procedure

At commencement of data collection, the senior physician and senior nurse of each participating PCICU will fill out the Gap Analysis Tool. All parents of infants hospitalized with CHD will be recruited after discharge from the PCICU, upon admission to the normal/intermediary care unit. The attending physician of the intermediary/normal care unit will check inclusion and exclusion criteria and provide oral and written study information to eligible parents. If parents decide to participate, the attending physician will obtain written informed consent from all parents with custody rights. The attending physician will then assess primary caregiver status by asking who took over most caregiving responsibilities (e.g., feeding, bathing, changing diapers) for the child during the past month. The primary caregiver will then receive the questionnaires and a return envelope. They will be asked to complete the questionnaires within 24 h after discharge from PCICU and hand it to one of the staff members of the unit in the sealed envelope, to ensure confidentiality. One of the investigators at each site will collect the returned questionnaires and hand them to a member of the research team not involved in the clinical care for the patients, for data entry. The principal investigator at each site will document the patient characteristics (infant age, gender) and medical information (e.g., diagnoses, duration of stay at PCICU, room size at PCICU) for each participating infant.

### Data Handling

We will use study participant numbers on all documentation to ensure confidentiality. All electronic study-related information will be stored on hospital servers in folders to which only members of the research team have access. One password-protected file linking study participant number and patient identification will be stored separately at each institution. Study information on paper will be kept in locked cabinets with restricted access. Data will be archived for 15 years after completion of data collection. We will conduct data entry in duplicate, in order to check for data entry mistakes. Principal and co- investigators will have access to final data files. Authorship of study reports will be assigned according to contribution to design, conduction, data analysis, interpretation and reporting of the results in writing and oral presentation. Study participants and funding institutions will be informed of the results at the end of the study period.

### Statistical Analyses

#### Power Analysis and Sample Size

Given the annual number of infants with congenital heart disease at the PCICUs of both centers, an inclusion of *N* = 2 × 140 families (140 families per center) is the maximum achievable number in the data collection period of 1 year. A power analysis was performed using G^*^Power for F-test for multivariate ANOVAs and in R for multilevel modeling using the R package “powerlmm.” Primary analyses are hypothesis generating. Secondary analyses are hypothesis confirming for variables on the parent level and hypothesis generating for variables on the child level. Effect sizes for our patient and age group could not be inferred from earlier studies or meta-analyses.

With an alpha level of 5%, a power of 0.80 and an upper bound total sample size of *N* = 2 × 140, the minimum effect size required for statistical detection in an ANOVA is Cohen's *d* = 0.34. This is considered to be a small-to-medium effect size. That same effect size would lead to an estimated power of 74% in a multilevel model with an alpha of 5%, and a total sample size of *n* = 2 × 140, assuming an intraclass correlation of 0.40, and 5,000 simulation runs. The minimum detectable multilevel effect size with a power of 0.80 is Cohen's *d* = 0.37.

#### Analysis Plan

Analysis will be performed in SPSS version 25/27 and R 4.0.2 with the packages “psych,” “mice”and “lmer.”

##### Preliminary Analyses

Given the expected sample size of 140 families for each PCICU, the Central Limit Theorem applies, rendering the assumption of normality in the predictor and/or outcome variables redundant. We will assess linearity of the association between parental FCC satisfaction and FCC adherence. Furthermore, we will assess equality of variances between centers on FCC satisfaction and FCC adherence. Missing data, if any, are evaluated for their origin, being Missing Completely At Random (MCAR), or either Missing At Random (MAR) or Not Missing At Random (NMAR) using Little's MCAR test to probe for the risk of bias in the main analyses (48). If missing values are missing completely at random, missing values are handled within the multilevel models through restricted maximum likelihood estimation. If data are MAR/NMAR, data will be multiply imputed before the main analyses (49). Results for all following analyses will be pooled over imputed datasets. Furthermore, we will report descriptive statistics of and analyze differences between centers concerning socio-demographic characteristics of the primary caregiver and infant medical characteristics.

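### When data pass as MCAR, the plan leaves missing values to REML, which with one record per family is complete-case analysis, and Little's test cannot justify that choice

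*Protocol article*

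**What the plan says.** The rule is in the Preliminary Analyses section of the protocol article. Little's MCAR test is used to judge the origin of any missing data, and two branches follow.

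- MCAR branch: "If missing values are missing completely at random, missing values are handled within the multilevel models through restricted maximum likelihood estimation".
- Other branch: "If data are MAR/NMAR, data will be multiply imputed before the main analyses". Results of the later analyses are then pooled over the imputed datasets.

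The features of the design that bear on this rule are:

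- The study is cross-sectional (Design), and one primary caregiver per infant completes one set of questionnaires (Procedure).
- Each parent and child outcome has its own series of models, with the PCICU as level two and adjustment for infant, medical and socio-demographic variables (Secondary Analyses).
- The primary analyses are two ANCOVAs, not multilevel models (Primary Analyses).
- The sample of 2 × 140 families "is the maximum achievable number in the data collection period of 1 year" (Power Analysis and Sample Size). No allowance for missing data is stated; the text speaks only of "Missing data, if any, are evaluated for their origin".

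**The concern.** Likelihood estimation makes use of incomplete subjects when a subject has other observed outcomes in the same model, as in a longitudinal study. That is not the case here, so the MCAR branch appears to promise a treatment of missing data that it does not deliver. Families with a gap in satisfaction or in any covariate are simply left out of the adjusted models.

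The route into that branch is a significance test whose non-rejection is read as evidence for MCAR. The route out of it sends MAR and NMAR data alike to imputation, although the standard form assumes MAR.

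At stake are precision in the confirmatory parent-level models, where the sample cannot be enlarged, and some bias in the satisfaction slope if missingness is related to distress.

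**Working it through.** **1. The plan's own figures.** Inputs from Power Analysis and Sample Size: alpha 5% (taken as two-sided), power 0.80, 140 families per centre, minimum detectable d = 0.34 for the ANOVA and 0.37 for the multilevel model, and 74% multilevel power at d = 0.34.

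- ANOVA: d × √(n/2) = 0.34 × √70 = 2.845, and Φ(2.845 − 1.960) = 0.812. The noncentral t gives 0.809, with a minimum detectable d of 0.336. The stated 0.34 is reproduced.
- Multilevel: 80% power at d = 0.37 means a signal of 1.960 + 0.842 = 2.802. At d = 0.34 it is 2.802 × 0.34/0.37 = 2.574, so power is Φ(0.614) ≈ 0.73, against 74% stated. The pair is consistent. The simulation behind it cannot be rerun, because its inputs are not all given.

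**2. What REML does with an incomplete family.** This step needs no assumption about rates.

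- Outcome missing: the family has no other record in that model and adds nothing to its likelihood.
- EMPATHIC-30 or a covariate missing: the row cannot be evaluated and is removed.

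As a check, a random-intercept REML model was fitted to 280 simulated families, of which 246 had complete rows. The fit used 246 families and gave a slope of −0.2983, the same as the fit to the complete rows alone.

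**3. Cost in precision (missing rates assumed).** With k variables each independently missing with probability p, the expected number of complete rows is 280 × (1 − p)^k. For k = 10:

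- p = 1%: 280 × 0.904 = 253
- p = 2%: 280 × 0.817 = 229
- p = 3%: 280 × 0.737 = 206
- p = 5%: 280 × 0.599 = 168

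Multilevel power at d = 0.37 after losing a share L of families is Φ(2.802 × √(1 − L) − 1.960), and the minimum detectable d is 0.37/√(1 − L). This takes power to depend on the number of families in the usual way.

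| Loss | Families per centre | ANOVA power, d = 0.34 | Multilevel power, d = 0.37 | Multilevel detectable d |
|---|---|---|---|---|
| 0% | 140 | 0.81 | 0.80 | 0.37 |
| 5% | 133 | 0.79 | 0.78 | 0.38 |
| 10% | 126 | 0.77 | 0.76 | 0.39 |
| 20% | 112 | 0.72 | 0.71 | 0.41 |
| 30% | 98 | 0.66 | 0.65 | 0.44 |

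**4. What Little's test detects.** Simulation with 280 families, ten correlated normal variables, a 0.05 test level and 10–20% missingness driven by the depression score; all of this is assumed. Share of runs in which the test did not reject:

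| Missing variable | Odds ratio per SD | No other missingness | 2% scattered missingness on each questionnaire score |
|---|---|---|---|
| Depression score itself | 1.5–2 | 50–89% | 86–95% |
| Depression score itself | 3 | 12–35% | 75–85% |
| Satisfaction score | 1.5–2 | 12–79% | 73–94% |
| Satisfaction score | 3 | 0–5% | 35–66% |

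**5. Bias of the complete-case slope.** The true slope was −0.20. The worst mean was −0.171 (satisfaction missing, odds ratio 3, 20% missing), an attenuation of 0.029/0.200 = 14.5%. Without other missingness, the test rejected in essentially every run of that scenario. At odds ratios of 1.5–2, the largest attenuation among runs that passed the test was (0.200 − 0.184)/0.200 = 8%.

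**The case against.** The strongest reply has four parts.

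- **Validity.** Under true MCAR, a complete-case analysis is unbiased and costs only precision. For a missing outcome, the likelihood of the observed rows is valid whenever missingness depends only on covariates in the model; imputation then gains only through auxiliary variables. Because models are run per outcome, a family missing one scale stays in the models for the others. All of this stands. It does not help with a missing EMPATHIC-30 score or covariate, where REML recovers nothing.
- **Size of the loss.** A reader might infer that the confirmatory analyses will lose a large part of the sample. The document does not support that: it gives no missing rate and no fixed list of covariates. Independence between gaps is also an unfavourable assumption. Basic infant and medical data are recorded by the site investigator, and gaps in a single questionnaire packet would tend to cluster in the same families. On the other side, every EMPATHIC-30 statement has a not-applicable box, so incomplete satisfaction scores are plausible.
- **Detection and bias.** A reader might infer that outcome-related missingness usually slips through and seriously distorts the slopes. That is too strong as well. Strong dependence in a single pattern is usually detected, and the attenuation seen was modest.
- **Detail.** The primary ANCOVAs are hypothesis generating and are covered if imputation is triggered. The content of the imputation model and sensitivity analyses are commonly left to an analysis plan. That is fair, and their absence is not the point. The point is a stated rule that does not do what it says.

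**Conclusion.** The point holds in a limited form. Two parts follow from the design and need no assumed rates: the MCAR branch is complete-case analysis with no stated method for the ANCOVAs, and a non-significant Little's test does not establish MCAR. It also follows from the usual MAR assumption that standard imputation does not remove NMAR bias, so the other branch claims more than it can deliver.

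The size of the consequences rests on assumptions. Precision is the surer cost: multilevel power at d = 0.37 of about 0.76 to 0.71 for a 10–20% loss, and no loss if the data are complete. Bias is the lesser concern, up to about 15% attenuation in the scenarios tried, and smaller where the test tends to pass. No single corrected figure can be given.

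**What to change.** Remove the test-based switch. State that multiple imputation is used for all analyses, the ANCOVAs included, whenever any model variable has missing values. The imputation model should contain all outcomes, EMPATHIC-30, the covariates and the unit. Keep Little's test as description only, and report complete-case results as a sensitivity analysis. Say plainly that the imputation assumes MAR; a delta-adjusted analysis for possible NMAR missingness is an optional addition.

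The cost is a few sentences in the plan and a little more programming. The package mice is already named in the Analysis Plan, and pooling over imputed datasets is already foreseen. No change to data collection or sample size is needed.

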##### Primary Analyses

In order to investigate differences between the two PCICUs concerning unit adherence to FCC and parent satisfaction with FCC, we will conduct two analyses of covariance (ANCOVA), accounting for relevant individual differences in socio-demographic and medical information as found from the descriptive analyses. First, we will conduct an ANCOVA with EMPATHIC-30 scores as the dependent variable, unit (Berlin, Bad Oeynhausen) as between-subjects factor, and scores on the Gap Analysis Tool as a covariate. Second, we will perform an ANCOVA of GAP Analysis Tool scores between units, with the EMPATHIC-30 scores as a covariate.

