##### Secondary Analyses

In order to investigate associations between parent satisfaction with FCC practices and parent, as well as infant outcomes, we will use multilevel models with PCICU as the level two factor. Such models account for shared exposure to unit characteristics, causing families within a unit to be more similar (to an unknown extent) compared to families from different units.

For the analysis of outcomes on the parent level, we will enter parent satisfaction with FCC as independent variable. Measures of parent well-being (specifically, symptoms of anxiety, depression, stress and parenting stress) will be entered as dependent variables. Extended models will be built to account for potential effects of infant characteristics (e.g., age and gender), medical variables (e.g., duration of stay at hospital, complexity of disease), as well as socio-demographic variables (e.g., employment status, ethnicity or professional background).

For each measure of parent well-being (symptoms of anxiety, depression, stress and parenting stress), a series of multilevel models is estimated. Each model in the set has incremental complexity. All models will be estimated using Restricted Maximum Likelihood, defining the covariance structure through variance components, and using the Huber- White sandwich estimator for the standard errors (50, 51).

For *each* parent well-being measure separately, the series of hypothesis confirming models is outlined below:

1) Model 1 estimates the unconditional means model for the parent well-being score.2) Model 2 estimates the conditional means model, adjusting for infant characteristics, medical and socio-demographic variables.3) Model 3 estimates the random intercept for the fixed slope association between FCC satisfaction and parent well-being, adjusted for infant characteristics, medical and socio-demographic characteristics.4) Model 4 estimates the random intercept and random slope for the association between FCC satisfaction and parent well-being, adjusted for infant characteristics, medical and socio-demographic characteristics.

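### The primary EMPATHIC-30 comparison takes its covariates from observed centre differences, which can leave predictors of satisfaction unadjusted

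*Protocol article*

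**What the plan says.** The Protocol article sets the rule in two steps. Under Preliminary Analyses, the investigators will "analyze differences between centers concerning socio-demographic characteristics of the primary caregiver and infant medical characteristics". Under Primary Analyses, the two ANCOVAs between units are then run "accounting for relevant individual differences in socio-demographic and medical information as found from the descriptive analyses". The first has EMPATHIC-30 as outcome and unit as factor, with "scores on the Gap Analysis Tool as a covariate".

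The article gives no test, no threshold and no definition of a relevant difference.

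The Secondary Analyses section works differently. It says "Extended models will be built to account for potential effects of infant characteristics", and goes on to medical and socio-demographic variables. These domains are illustrated by examples and do not depend on what the centre comparison shows.

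On status, Power Analysis and Sample Size states that "Primary analyses are hypothesis generating".

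**The concern.** Families are not allocated to units at random, so covariate adjustment is the only stated protection of the unit comparison against differences in case mix. Confounding by a variable depends on two things: how far it differs between units, and how strongly it predicts satisfaction. A rule driven by observed centre differences looks at the first and, as written, says nothing about the second. A strong predictor with a small observed imbalance can be left out, while an imbalanced but irrelevant variable is kept.

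The choice is also made after looking at the data, so the reported p-values and intervals treat a selected model as if it had been fixed. A difference in case mix could then be read as a difference in care. That matters because the Discussion expects the results to point to changes at the two centres and perhaps to apply elsewhere.

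**Working it through.** **Inputs from the Protocol article (Power Analysis and Sample Size).** "140 families per center", alpha 5%, power 0.80, and "the minimum effect size required for statistical detection in an ANOVA is Cohen's *d* = 0.34".

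**Inputs that are assumptions.** Selection by a two-sided t-test at p<0.05, the number of confounders, their imbalance and their slopes. The article gives none of these.

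**Step 1: the plan's own figure.** With n = 140 per unit the noncentrality is d × √(n/2) = 0.34 × √70 = 2.845 on 278 degrees of freedom. Power is 0.809, and power 0.80 is reached at d = 0.336. The stated 0.34 reproduces.

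**Step 2: how often a true imbalance would be missed.** The same formula is applied to a covariate.

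| True imbalance (SD) | Noncentrality | Detected | Missed |
|---|---|---|---|
| 0.1 | 0.837 | 13% | 87% |
| 0.2 | 1.673 | 39% | 61% |
| 0.3 | 2.510 | 71% | 29% |
| 0.4 | 3.347 | 92% | 8% |

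**Step 3: effect on the unit contrast.** With no adjustment, the bias is the sum over confounders of slope × imbalance. For four at 0.2 SD and slope 0.3 this is 4 × 0.3 × 0.2 = 0.24 SD. Selection removes part of it. The size of the remainder comes from simulation: 4,000 runs per setting, 140 per unit, no true unit effect, outcome SD 1 within unit, independent confounders, Gap score left out.

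| Confounders | Imbalance (SD) | Slope | Bias after selection (SD) | Type I error |
|---|---|---|---|---|
| One | 0.2 | 0.5 | 0.040 | 5.6% |
| Four, same direction | 0.2 | 0.15 | 0.046 | 6.8% |
| Four, same direction | 0.2 | 0.2 | 0.064 | 8.1% |
| Four, same direction | 0.2 | 0.3 | 0.092 | 11.7% |
| Four, same direction | 0.3 | 0.3 | 0.057 | 9.0% |
| Four, same direction | 0.4 | 0.3 | 0.019 | 5.7% |
| Three one way, one the other | 0.2 | 0.3 | 0.044 | 6.3% |
| Two each way | 0.2 | 0.3 | 0 | 4.6% |

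Across all single-confounder settings (imbalance 0.1 to 0.4 SD, slope 0.2 to 0.5), type I error was 4.5% to 6.1%. Where every true confounder was entered regardless of imbalance, bias was within 0.005 SD of zero and type I error was 4.3% to 5.8%.

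**Step 4: scale.** The largest bias in the table is 0.092 / 0.34 = 27% of the detectable effect. That setting implies that the four confounders explain 4 × 0.3² = 36% of the variance in satisfaction within a unit. At slope 0.15 the figure is 4 × 0.15² = 9%.

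**Step 5: the Gap score.** Under Procedure, the Gap Analysis Tool is completed for each unit by its senior physician and senior nurse at the start. Attached to families, the score is constant within a unit. If the two units' scores differ, it is perfectly collinear with the unit factor and the unit effect cannot be estimated. If they are equal, it adjusts for nothing. The simulated model is therefore the planned one only after this covariate is taken out.

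**The case against.** A reader might infer that confounders which fail a significance test will be left out and that the comparison is therefore biased. The article does not support that. It gives no test or threshold, and a relevant difference could mean one judged by size or by prognostic importance. Bias also needs an omitted variable that both differs between units and predicts EMPATHIC-30. This objection stands, and every figure from Step 2 on is conditional on the assumed rule.

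A reader might also infer that 140 per unit would miss most moderate imbalances. It would not: 0.3 SD is detected 71% of the time and 0.4 SD 92%. Only small imbalances, about 0.2 SD or less, are mostly missed.

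The 12% figure needs four fairly strong confounders all acting the same way, and nothing in the article suggests that this is likely. Selection is also better than no adjustment: with one confounder at 0.2 SD and slope 0.5, bias falls from 0.100 to 0.040 SD.

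Finally, the comparison is declared hypothesis generating, and a condensed article may leave an exact covariate list to a fuller plan. The first of these lowers the stakes without removing confounding. The second does not answer the point, because the article does not leave the choice open: it states a rule based on observed centre differences.

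**Conclusion.** The point holds in a limited form. The covariates of the primary EMPATHIC-30 comparison are to be chosen from observed centre differences by an undefined criterion. In a non-randomised comparison this can leave residual confounding and yields p-values that ignore the selection. It does not follow that the comparison is biased.

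Under an assumed p<0.05 rule the harm is small in most of the settings examined. It becomes material, at 8% to 12% type I error, when several confounders with slopes of 0.2 to 0.3 act in one direction and each has a small or modest imbalance. These sizes and slopes are illustrations, not estimates. Given the hypothesis-generating status, this is a minor-to-moderate improvement and not a defect that invalidates the study.

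**What to change.** In Primary Analyses, replace the reference to the descriptive findings with a covariate set fixed in advance on prognostic grounds and entered whatever the centre comparison shows. Keep that comparison as description only.

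The set can be drawn from variables already collected and from the domains that Secondary Analyses illustrates. That section gives examples, not a closed list, so the set has to be written out. One possibility is:

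- infant age and gender;
- disease complexity (Aristotle score) or CHD severity class;
- caregiver education or employment;
- migration background or first language.

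State also whether duration of stay is included or is treated as a possible consequence of unit care.

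In the same edit, remove the Gap Analysis Tool score as a covariate from this ANCOVA. Without that, the unit effect is not estimable when the units' scores differ, whichever other covariates are chosen.

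The cost is a short change of text and a few of about 278 degrees of freedom (280 − 2). With 8 to 10 covariate terms, 268 to 270 would remain. No new data are needed.

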## Methods and Analysis

### Design

This two-center cross-sectional study will be conducted at two PCICUs of two specialized pediatric cardiac centers in Germany (Berlin, Bad Oeynhausen).

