#### Unit Adherence to FCC Practices

We will use the Gap Analysis Tool provided by the Society of Critical Care Medicine (SCCM) Guidelines for Family-Centered Care in the ICU (35). This tool comprises all 24 recommendations of the guidelines by the SCCM, which are rated to indicate how frequently the ward already implements each recommendation as follows: 0 (nearly always), 1 (usually), 5 (sometimes), 10 (nearly never). For recommendations only applicable to neonatal ICUs, a “not applicable” option is available. Each score is transferred into an item score by multiplying the frequency score by outcome points, which are specified for each recommendation. Outcome points range from 1 to 5 depending on the importance of the particular outcome the recommendation targets. Accordingly, item scores range from 0 to 50.

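### Neither primary ANCOVA can be run as written, because the Gap Analysis Tool score belongs to the unit and does not vary between families

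*Protocol article*

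**What the plan says.** Under Design, the study takes place at "two PCICUs of two specialized pediatric cardiac centers in Germany". Under Unit Adherence to FCC Practices, the Gap Analysis Tool has 24 recommendations, "which are rated to indicate how frequently the ward already implements each recommendation". Each frequency score runs from 0 (nearly always) to 10 (nearly never) and is multiplied by outcome points, so a higher score means poorer adherence. Under Procedure, the timing and the raters are fixed: "At commencement of data collection, the senior physician and senior nurse of each participating PCICU will fill out the Gap Analysis Tool". EMPATHIC-30, by contrast, is a parent self-report, one per family.

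Under Primary Analyses, two ANCOVAs are planned. The first has "EMPATHIC-30 scores as the dependent variable, unit (Berlin, Bad Oeynhausen) as between-subjects factor, and scores on the Gap Analysis Tool as a covariate". For the second, "we will perform an ANCOVA of GAP Analysis Tool scores between units, with the EMPATHIC-30 scores as a covariate". Both are to be run "accounting for relevant individual differences in socio-demographic and medical information as found from the descriptive analyses".

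Under Preliminary Analyses, the linearity of satisfaction against adherence is to be checked, and "we will assess equality of variances between centers on FCC satisfaction and FCC adherence".

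**The concern.** The two ANCOVAs treat adherence as if each family had its own value. The data collection yields one value per unit, or at most two if the physician and the nurse each complete a form. Nothing in the article describes a Gap score per family or a repeated one.

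The two models then fail for different reasons. In the first, the covariate carries the same information as the unit factor, so their effects cannot be separated. In the second, the dependent variable has no spread within a unit, so there is no error variance against which to test a unit difference.

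These two models are the whole of the primary analysis. Software will often drop the redundant term in the first model without stopping, and an unadjusted difference between centers could then be published as adjusted for adherence. The second model would give either no test or, if scores are spread over families, a spurious one.

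**Working it through.** **Inputs.** Two units (Design); 140 families per unit, 280 in total, alpha 5%, power 0.80, stated minimum detectable d = 0.34 (Power Analysis and Sample Size); Gap score per ward, rated by two senior staff at study start (Procedure); EMPATHIC-30 once per family.

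**The plan's own figure.** For a plain two-group comparison, minimum detectable d = (1.960 + 0.842) × √(2/140) = 2.802 × 0.1195 = 0.335. The exact noncentral t gives 0.336, and power at d = 0.34 is 0.81. The stated 0.34 therefore reproduces, but for a comparison of units without the Gap covariate.

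**ANCOVA 1: EMPATHIC-30 on unit and Gap.** Code unit as 0 or 1 and let the unit scores be g0 and g1. For every family, Gap = g0 + (g1 − g0) × unit. The Gap column is a linear combination of the intercept and unit columns, so [intercept, unit, Gap] has rank 2 of 3.

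An illustration used 280 simulated families, arbitrary scores of 200 and 260, and infant age as an extra covariate:

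| Model | Residual SS |
|---|---|
| unit + Gap + age (4 columns, rank 3) | 87.06 |
| unit + age | 87.06 |
| Gap + age | 87.06 |

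The sum of squares for unit given Gap is 0, and so is that for Gap given unit. The result does not depend on the scores chosen, as long as they differ. If the two units happened to score the same, Gap would be a constant, again rank 3 of 4. Unit would then be testable, but nothing would have been adjusted for.

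**ANCOVA 2: Gap on unit and EMPATHIC-30, one score per unit.** The design has full rank, so this is not collinearity. The fit is exact: in the illustration the intercept is 200, the unit coefficient is 60 (simply 260 − 200), the EMPATHIC-30 slope is 0, and the residual SS is 0 to machine precision. F divides by an error mean square of 0 and is undefined.

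**Do two raters or 24 items help?** With 4 rater rows or 48 item rows (24 × 2), EMPATHIC-30 can enter only as a unit mean, because no family belongs to a rater or an item. The columns intercept, unit and mean EMPATHIC-30 then have rank 2 of 3, and unit is aliased again.

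**If rater scores were copied onto families.** Assume four independent rater scores with no true unit difference, each copied onto 70 families.
- Let t4 be the correct t statistic on 4 observations (2 df). The pooled variance on the copied data is (140/278) times the one in t4, and the standard error uses 2/140 in place of 2/2. Hence t(copied) = t4 × √139 = 11.79 × t4.
- The nominal test rejects when |t4| > 1.97/11.79 = 0.167.
- For t on 2 df, P(|t| > x) = 1 − x/√(2 + x²) = 1 − 0.167/1.424 = 0.883.

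Simulation (20,000 runs) gave 88.2%. The rate is higher if the two raters of a unit share a common component. If they complete one joint form, or are averaged, there is no test at all.

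**Preliminary checks.** With one adherence value per unit, the within-center variance of adherence is 0 in both centers. Satisfaction is then observed at only two adherence values, through which a straight line always fits the means. Neither check can tell the analyst anything.

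**The case against.** The strongest defence is that the primary analyses are declared hypothesis generating, that a journal article condenses the full plan, and that the satisfaction question itself is not lost. Part of this stands. The unit comparison of EMPATHIC-30 without the Gap score is estimable with the same data, so what fails in the first model is the adherence-adjusted comparison. The confirmatory parent-level models do not use the Gap score and are untouched. The hypothesis-generating label relaxes error control, but it does not identify a parameter. Nor could a fuller document supply family-level Gap scores from a tool that rates the ward.

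Other reservations are fair:

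- The 88% depends on a use of the rater scores that the article does not describe. It also does not say whether physician and nurse complete one form or two. The figure shows what a workaround would do and is not a forecast.
- The article defines Gap item scores but no total. A variance across items could be computed, but it would not be the variance that an ANCOVA of families needs.
- Whether satisfaction differs beyond measured adherence is a coherent question. Two units cannot answer it.
- Choosing covariates from observed differences is a separate and weaker point, since a covariate list is often left to the analysis plan and these analyses are exploratory. It has no bearing on estimability.

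**Conclusion.** The concern holds and needs correction before analysis. The first ANCOVA is not identified (rank 2 of 3). The second is degenerate (residual SS of 0, no F-test). The preliminary checks involving adherence fail because adherence does not vary between families. The conclusion is structural: it follows from a ward-level score and two units, and not from sample size, effect size or the score values. It assumes only what Procedure implies, that no family-level or repeated Gap score is collected. The false-positive rate of about 88% applies only if separate, independent rater scores are copied onto families.

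**What to change.** 1. Compare EMPATHIC-30 between units with unit as the only factor and a short list of family-level covariates named in advance from data already collected, for example CHD severity class, infant age and caregiver education. Leave out the Gap score. Duration of PCICU stay is also available, but it may reflect unit practice, so its place in the main or a sensitivity analysis should be justified.
2. Report the Gap Analysis Tool descriptively: item scores by unit, the difference between units and, if separate forms are used, scores by rater and rater agreement. State whether one form or two are completed per unit, and that a higher score means poorer adherence. Make no significance test.
3. Delete the linearity check of satisfaction against adherence and the equal-variance check for adherence. The equal-variance check for satisfaction can stay.

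The cost is wording in the analysis plan; no new data are needed. The study gives up an inferential test of adherence that two units could never have supported. The stated detectable effect of d = 0.34 then refers to the satisfaction comparison that is actually made.
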